#### Exposures and Outcomes

We considered the exposure as continuous anticoagulant prescription for the first time after receiving an AF diagnosis. Although almost all anticoagulant prescriptions in the United Kingdom are issued from primary care if an anticoagulant is started in a hospital, we measured exposure from the first general practice prescription. We excluded patients who had an interval of greater than 90 days between anticoagulant prescriptions.

Outcomes are first records of stroke and all-cause mortality based on previously published Read codes [16,17] Stroke was included regardless of etiology, an approach used in other studies [18,19]. Study participants were followed for stroke and all-cause mortality till the end of the study period.

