The aim of this study is to understand the disease and prescribing trends related to AF in general practice. We also aim to develop a system to monitor practice-level indicators for AF of the same trends and evaluate the usability of this system. The primary objective of this study is to investigate if people with newly diagnosed AF treated with DOACs versus warfarin have any difference in stroke or all-cause mortality in long-term follow-up. The secondary objectives of this study are to develop an AF dashboard as an intervention method at a practice level and to evaluate the usability of the AF dashboard.

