### Statistical Analysis

Analysis of data extracted from general practice CMR was carried out using the statistical software R. We studied the influence of the anticoagulation regimen by evaluating the cause-specific hazard ratio and the subdistribution hazard ratios of both events. Additionally, we estimated cumulative incidence for both events by direct regression, utilizing the inverse of the probability of censoring weights method [15] with time-varying effects [20]. We will report and interpret both cause-specific and subdistribution analyses. The cause-specific hazard ratio is often interpreted as estimating etiological association, estimating associations between covariates, and the rate at which events occur in those participants who are event-free. The cause‐specific hazard ratio can be interpreted as a rate ratio. Whenever the proportional hazards assumption was violated, we interpreted all hazard ratios as time-averaged effects.

We will determine the (adjusted) incidence and prevalence of AF for each year along with the proportion of incident and prevalent cases treated with nothing, antiplatelet medications only (eg, aspirin), and anticoagulant therapy (warfarin/types of DOACs). We will also determine the number of strokes, transient ischemic attacks, deaths, and bleeds in the incident and prevalent cases per year.

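### As worded, the 90-day rule excludes patients who pause and restart but does not catch those who stop for good, so the cohort is neither continuously exposed nor an initial-drug cohort

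*Protocol article*

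**What the plan says.** The primary objective, at the end of the Introduction, is whether people with newly diagnosed AF "treated with DOACs versus warfarin have any difference in stroke or all-cause mortality in long-term follow-up".

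Methods, Phase 1, Exposures and Outcomes sets the exposure and the follow-up:

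- Definition: "We considered the exposure as continuous anticoagulant prescription for the first time after receiving an AF diagnosis".
- Start: "we measured exposure from the first general practice prescription".
- Continuity: "We excluded patients who had an interval of greater than 90 days between anticoagulant prescriptions".
- End of follow-up: "Study participants were followed for stroke and all-cause mortality till the end of the study period".

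No end of exposure is stated, and nothing is said about the time after a patient's last prescription. Statistical Analysis then describes "evaluating the cause-specific hazard ratio and the subdistribution hazard ratios of both events", by anticoagulation regimen. It adds a cumulative incidence regression with inverse-probability-of-censoring weights and time-varying effects. Neither feature is described as handling the stopping of treatment.

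**The concern.** An interval between two prescriptions needs the second one to close it. A patient who never returns cannot produce an interval longer than 90 days, and a patient with one prescription produces no interval at all. The rule thus works against its apparent purpose: it drops people who came back to treatment and keeps people who left it.

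Two consequences follow if the text is applied as it stands. Strokes and deaths in years without anticoagulation would be attributed to the first drug. The estimate would also answer neither of the two questions that a reader could put to it. It is not the effect of continuous use, because stopped time is included. It is not the effect of starting one drug rather than the other, because some starters are removed for what happened later. Both matter for the primary comparison, and more so the longer the follow-up.

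**Working it through.** The article gives no Phase 1 sample size, event rate or stopping rate, so there is no stated figure to reproduce. There are two checks. The first uses only the written rule; the second rests on assumed rates.

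**1. The rule applied to four invented prescription histories.** Follow-up is 1,825 days (5 years) with prescriptions every 28 days. The rule as written excludes a patient if any difference between successive prescription dates exceeds 90 days. The last column shows exposed follow-up if it were instead cut 90 days after the last prescription before any gap longer than 90 days, with the open final interval counted as a gap.

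| History | Rule as written | Days followed as written | Exposed days if cut at 90 |
|---|---|---|---|
| Prescriptions throughout | kept | 1,825 | 1,825 |
| Stops for good after day 364 | kept | 1,825 | 364 + 90 = 454 |
| Single prescription at day 0 | kept | 1,825 | 90 |
| Gap from day 364 to day 484 (120 days), then restarts | excluded | 0 | 364 + 90 = 454 |

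The second and fourth patients have the same record up to day 454. The rule as written keeps the one who never returned, with 1,825 − 454 = 1,371 days (75% of follow-up) beyond the 90-day allowance. It removes the one who did return. The second and third patients do not meet the article's own definition of exposure.

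**2. Illustration of the effect on the ratio (all inputs assumed).** Set the on-warfarin stroke rate to 1. Let R be the true on-treatment ratio, DOAC to warfarin. Let k be the rate after stopping, from 1.5 to 3 and the same in both groups. Let p be the share of person-time after permanent stopping. The crude rate ratio is then

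(R(1 − pD) + pD·k) / ((1 − pW) + pW·k).

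*Equal stopping, R = 0.80:*

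- p = 0.20: k = 1.5 gives 0.94/1.10 = 0.85; k = 3 gives 1.24/1.40 = 0.89.
- p = 0.40: k = 1.5 gives 1.08/1.20 = 0.90; k = 3 gives 1.68/1.80 = 0.93.

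*No true difference, R = 1:*

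- pD = 0.20, pW = 0.30: 1.10/1.15 = 0.96 to 1.40/1.60 = 0.88.
- pD = 0.30, pW = 0.20: 1.15/1.10 = 1.05 to 1.60/1.40 = 1.14.

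A two-state model (on treatment, then stopped) gives the same picture. It assumes an on-warfarin rate of 0.015 per year, the same range of k, and 3 or 5 years of follow-up:

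| True ratio | Stopping per year | Ratio seen |
|---|---|---|
| 0.80 | 5% in both | 0.82–0.85 |
| 0.80 | 15% in both | 0.85–0.91 |
| 0.80 | 30% in both | 0.89–0.94 |
| 0.80 | DOAC 15%, warfarin 30% | 0.73–0.81 |
| 0.80 | DOAC 30%, warfarin 15% | 0.945–1.16 |
| 1.00 | DOAC 15%, warfarin 30% | 0.81–0.94 |
| 1.00 | DOAC 30%, warfarin 15% | 1.07–1.23 |

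If follow-up is censored at stopping, the ratio returns to 0.80 or 1.00, provided that stopping is non-informative. These are crude rate ratios, not the cause-specific or subdistribution hazard ratios that the plan will report. Neither model represents the removal of returners.

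**The case against.** The strongest reply is that the article never says permanent stoppers are analysed as exposed. A patient with one prescription and years without treatment fails the stated definition on its face. The 90-day sentence may be a further exclusion rather than the only means of enforcing it. A condensed article can also leave the end of exposure and the censoring events to a fuller document. This stands as a limit on the point. A reader might infer that stoppers were certainly counted as exposed and that the results are biased; the text does not show this. It shows only that the rule as worded does not reach these patients and that no other stated rule does. It is still more than silence, because the rule that is printed treats returners and permanent stoppers in opposite ways.

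A second reply is that following every starter to study end is a legitimate initial-drug analysis, so dilution is a bias only against an on-treatment effect. This also stands. A reader might infer that the problem would persist even if nobody were excluded for a gap. It would not: only the label of continuous exposure would then be wrong. The incoherence comes from combining the gap exclusion with unrestricted follow-up.

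Third, the magnitudes have no anchor in the document. That is correct. The Introduction says that DOACs, unlike warfarin, need no monitoring, which makes unequal stopping conceivable, but it says nothing about stopping rates.

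**Conclusion.** The point holds as a defect in how the continuity rule is worded and combined with follow-up to study end. Applied literally, it yields a cohort that does not match its own definition of exposure and is not an initial-drug cohort either. Nothing in Statistical Analysis repairs this.

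That untreated time is attributed to the first drug is an inference from the lack of any stated end of exposure. Relative to an on-treatment effect, the bias would be towards 1 with equal stopping and in either direction with unequal stopping, assuming the same event rate after stopping in both groups. Its size cannot be derived from the document, and the ranges above only show that it need not be trivial. The correction is worth making because it is cheap relative to the ambiguity it removes.

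**What to change.** Apply the 90-day rule symmetrically, by censoring instead of excluding.

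- **Continuous-exposure analysis:** end exposed follow-up 90 days after the last prescription that precedes any gap of more than 90 days. Treat the open interval after the final prescription as a gap in the same way. Count events within those 90 days for the drug. Patients with a later gap stay in up to that point.
- **Initial-drug analysis:** report beside it an analysis of all starters, including those with gaps, followed to study end and labelled as such.
- **If the final open interval was already counted:** say so, and state how those patients were handled. That would settle the main ambiguity.

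The dates come from prescriptions already held. The cost is not nil: there is less exposed follow-up, and intervals are wider. Censoring at stopping may be informative, for example when a bleed leads to stopping. Any weights for stopping therefore need predictors updated over time, such as recorded bleeds. Covariates describes comorbidities at baseline and lists no bleeding history, so the existing weights cannot simply be extended. The initial-drug analysis serves as the check. Results states that the Phase 1 analysis was completed in December 2019, so this means a rerun and a clarified definition, not only a change of text.

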**Methods:**

The study was conducted in 2 phases. The initial phase was a quantitative analysis of routinely collected primary care data from the Oxford Royal College of General Practitioners Research and Surveillance Center (RCGP RSC) sentinel network database. AF cases from 2009 to 2019 were identified. The study investigated the impact of the use of anticoagulants on complications of AF over this time period. We used this dataset to examine how AF was managed in primary care during the last decade. The second phase involved development of an online dashboard for monitoring management of AF in general practice. We conducted a usability evaluation for the dashboard to identify usability issues and performed enhancements to improve usability.

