## Introduction

Atrial fibrillation (AF) is one of the commonest arrhythmias observed in clinical practice [1]. Globally, the incidence of AF is rising. The thromboembolic complications of AF can lead to significant disabling consequences for patients, including transient ischemic attack, stroke, and pulmonary embolism. Early recognition of AF in general practice can lead to early intervention with managing the risks of these complications.

Current guidelines on the management of AF by the National Institute for Health and Care Excellence (NICE) advise identifying and managing the underlying causes of AF, treating the arrhythmia, and assessing and managing the risk of stroke in these patients [2]. Risk of stroke is determined by the CHA_2_DS_2_-VASc (Congestive heart failure, Hypertension, Age, Diabetes, previous Stroke/transient ischemic attack–VAScular disease) assessment tool [3], which guides the practitioner on commencing anticoagulation treatment to manage this risk. The risk of starting a patient on anticoagulation is assessed using the HAS-BLED (Hypertension, Abnormal renal/liver function, Stroke, Bleeding history or predisposition, Labile international normalized ratio, Elderly, Drugs/alcohol concomitantly) score, assessing for major bleeding risks [4].

Anticoagulation therapy aims to reduce the risk of thromboembolic events. This has been achieved using warfarin (a vitamin K antagonist) for many years. The introduction of direct oral anticoagulants (DOACs) such as apixaban and rivaroxaban to clinical practice has changed how AF is managed in clinical practice [5]. In comparison to warfarin, DOACs are observed to have similar or better mortality and vascular outcomes [6]. They have the added benefit of requiring no monitoring, as opposed to warfarin use [7]. Though studies have highlighted that increased number of patients in clinical practice are receiving treatment for AF [8], whether they are managed according to national or local guidelines is unclear. Better understanding of current management trends of AF in population will guide practitioners on how best to employ interventions in clinical practice to increase awareness of AF and early recognition.

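### Excluding whole patients for a prescription gap after time zero inflates mortality rates, and biases the DOAC–warfarin hazard ratio for death whenever gap rates or follow-up differ by drug

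*Protocol article*

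**What the plan says.** All three rules are in the protocol article, Methods, Phase 1, Exposures and Outcomes.

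- Exposure: "We considered the exposure as continuous anticoagulant prescription for the first time after receiving an AF diagnosis". Its start is fixed by "we measured exposure from the first general practice prescription".
- Exclusion: "We excluded patients who had an interval of greater than 90 days between anticoagulant prescriptions".
- Follow-up: "Study participants were followed for stroke and all-cause mortality till the end of the study period".

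The comparison served is the primary objective in the Introduction: to "investigate if people with newly diagnosed AF treated with DOACs versus warfarin have any difference in stroke or all-cause mortality in long-term follow-up". Statistical Analysis plans cause-specific and subdistribution hazard ratios for both events, plus cumulative incidence by direct regression with inverse probability of censoring weights. The article gives no gap rate, event rate, or follow-up time by drug.

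**The concern.** An interval between prescriptions can only arise after the first prescription, which is time zero. The rule removes the patient, not the person-time after the gap, so whether someone is in the cohort at day 0 depends on their later history.

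For death the selection runs one way. A patient who dies at month 2 has almost no time to build a gap of more than 90 days and is nearly always kept. A patient with a gap at year 4 loses four years of survival that should count in the denominator. More survival time is lost where follow-up is longer or stopping is commoner.

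The Introduction gives reasons to expect both to differ by drug. On warfarin it says "This has been achieved using warfarin (a vitamin K antagonist) for many years", with DOACs arriving later, so within a window where "AF cases from 2009 to 2019 were identified" warfarin starters should tend to have longer follow-up. On DOACs it says "They have the added benefit of requiring no monitoring, as opposed to warfarin use", so prescribing patterns may differ too. At stake is a spurious mortality benefit or harm in the primary comparison.

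**Working it through.** There is no figure in the article to reproduce. All rates below are assumptions, chosen to show how the rule behaves.

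**Set-up.** Constant event hazard L, gap hazard D independent of events, follow-up τ, and k = L + D. A patient is kept if no gap occurs before the event or τ, which is the natural reading when the event is death. Per starter:

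- events among the kept = (L/k)(1 − e^(−kτ))
- person-years among the kept = L[(1 − e^(−kτ))/k² − τe^(−kτ)/k] + τe^(−kτ)
- proportion kept = events + e^(−kτ)

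With L = 0.05/yr and a true hazard ratio of 1:

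| D (/yr) | τ (yr) | Events | Person-years | Rate | Kept |
|---|---|---|---|---|---|
| 0.15 | 6 | 0.1747 | 2.2289 | 0.0784 | 48% |
| 0.15 | 2.5 | 0.0984 | 1.6291 | 0.0604 | 70% |
| 0.20 | 5 | 0.1427 | 1.7168 | 0.0831 | 43% |
| 0.10 | 5 | 0.1759 | 2.7471 | 0.0640 | 65% |

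**Follow-up differs, gap rates equal** (rows 1 and 2; warfarin 6 years, DOAC 2.5): 0.0604/0.0784 = 0.77.

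**Gap rates differ, follow-up equal** (rows 3 and 4): warfarin 20%, DOAC 10% gives 0.0640/0.0831 = 0.77. The reverse gives 0.0831/0.0640 = 1.30.

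**Cumulative incidence.** True 5-year risk is 1 − e^(−0.25) = 22.1% in both arms. Among the kept it is 0.1427/0.4292 = 33.2% (D = 0.20) and 0.1759/0.6482 = 27.1% (D = 0.10).

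**The planned hazard ratio.** Among kept patients with R years of follow-up remaining, the hazard is L / [(L/k)(1 − e^(−kR)) + e^(−kR)]. This exceeds L whenever D and R are above zero, and rises with both. In the 6 v 2.5 year case:

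- at time 0: warfarin 0.05/0.4759 = 0.1051, DOAC 0.05/0.7049 = 0.0709, ratio 0.67
- at 2.5 years: warfarin (R = 3.5) 0.05/0.6224 = 0.0803, DOAC (R = 0) 0.0500, ratio 0.62

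A Cox fit averages these to about 0.65, further from 1 than the crude 0.77, because it compares patients at the same time since starting.

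**Simulation over a wider range** (Cox, true hazard ratio 1, 60,000 per arm, event hazard 0.06 or 0.015/yr):

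- warfarin gap rate 0.15 to 0.30 v DOAC 0.10: hazard ratio 0.89 down to 0.59
- warfarin 0.10 v DOAC 0.20: 1.28 to 1.30
- equal gap rates (0.1 or 0.2), follow-up up to 10 years on warfarin v up to 5 on DOAC: 0.67 to 0.87
- equal gap rates and equal follow-up: 0.97 to 1.01, although rates in both arms are inflated (for example 7.7 against a true 6.0 per 100 person-years)
- every starter kept: 0.98 to 1.05; censored at the gap: 0.97 to 1.04

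**Stroke.** A non-fatal stroke does not end the prescription record, and the rule does not say the gap check stops at the stroke. If later gaps also exclude and are independent of stroke, selection does not depend on the event, the rate stays at L and the ratio at 1. If stroke leads to stopping, stroke cases are removed preferentially and the rate is pushed down. If the check stops at the stroke, the table above applies.

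**The case against.** **The bias in the ratio is conditional.** This stands. A reader might infer that the hazard ratio is biased whatever the data look like. It is not: with equal gap rates and equal follow-up it stays near 1. The Introduction makes a difference likely but supports no size, and the illustrations run in both directions.

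**Stroke is not death.** This also stands. A reader might infer that early stroke patients are always retained and that stroke rates are inflated in both arms. The text supports neither, because it does not say whether gaps after a non-fatal stroke count.

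**Switching.** A reader might also infer that patients who move from warfarin to a DOAC without a gap are analysed under the first drug. The article does not say so, and a condensed article may leave this to the full protocol. Dilution from switching would in any case be present in an as-started analysis too.

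**The censoring weights deal with it.** They do not. They act on censoring among retained patients and cannot restore people already removed. They are also attached only to the cumulative-incidence regression, not to the hazard ratios.

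**The authors may have meant an early window, or censoring at the gap.** Possibly, but the sentence excludes patients, sets no time limit, and stands beside follow-up to study end. This is a stated rule rather than an omitted detail, and if something else was meant it needs correcting.

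**Conclusion.** The concern holds in a conditional form. As written, the exclusion selects the cohort on events after time zero. For death, it inflates rates and cumulative incidence among retained patients, and it biases the hazard ratio under the null whenever gap rates or available follow-up differ between drugs. For stroke, neither size nor direction can be established from the text.

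Under the assumed rates, a true ratio of 1 appears as anything from about 0.6 to 1.3. The range rests on constant hazards, gaps independent of events, and gaps counted only before the event. It shows that the rule can create an apparent benefit or harm; it does not estimate the bias in this study, which needs gap rates and follow-up by drug.

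**What to change.** Delete the exclusion. Keep every initiator from the first prescription, and make this as-started analysis the basis of the primary hazard ratios.

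Add an on-treatment analysis that censors at the date the 90-day gap is reached. Apply weights for stopping to the hazard-ratio models as well as to cumulative incidence. State that this analysis relies on stopping being explained by the modelled covariates: censoring at the gap recovered the truth above only because gaps were made independent of events. The Covariates section lists comorbidities at baseline, so time-varying predictors of stopping may have to be added.

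Report the number with a gap and the follow-up time by drug, so that readers can judge how far the two analyses should differ.

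Cost: a change to one rule, a rerun, and some extra variance from the weights. The rerun needs the excluded patients' records, and the article does not say whether the extract kept them. It reports the phase 1 analysis complete in December 2019 and publications under review by October 2020, so the change may have to be made as a correction to those reports.

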#### Covariates

We included variables likely to be used as indicators in prescribing anticoagulants: age-band, gender, and deprivation reporting Index of Multiple Deprivation (IMD) quintile. IMD is a national measure of socioeconomic status, which can be derived at an individual level from first part of postcode. We adjusted for comorbidities from that part of the stroke risk score (CHA_2_DS_2_-VASc), namely, heart failure, hypertension, stroke or transient ischemic attack, and myocardial infarction or peripheral vascular disease at baseline. We also included smoking status as a covariate.

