### Phase 1: Quantitative Analysis of AF Data

#### Data Source

The initial phase involved a repeated cross-sectional retrospective analysis of data extracted from the RCGP RSC database, a surveillance network, which collects data from computerized medical records (CMR) from more than 3.5 million patients and over 300 general practices in England. CMRs are used during consultations to record patient conditions and prescriptions [12,13]. Anonymized clinical coded data from participating general practices were uploaded weekly to a secure network at the Clinical Informatics Research Group [12,14]. This study used NICE guidelines as the standard to compare the management of AF across this database.

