## Discussion

The RCGP RSC sentinel network has a large dataset, which is representative of information regarding primary care practices on management of AF. The quantitative analysis will report on the current trends of anticoagulant prescribing using a real-world data set in the United Kingdom and the overall population effect of the use of DOAC use.

Missing/incomplete data could be a potential issue in this analysis. We intend to reduce the effect of this issue by incorporating an ontological approach, considering practice level variations in the anticoagulation prescribing.

The qualitative analysis of the dashboard will indicate the priority of sections that require an improved user experience. We intend to enhance the dashboard using the outcomes of the usability study and deploy to general practices in the RCGP RSC sentinel network.

As the incidence of AF has increased over the years, there is a greater focus on early recognition of AF in general practice to allow for early intervention. This study will give insights into the current trends in management of AF using real-world data from the Oxford RCGP RSC database. We anticipate that the outcomes of this study will be used to guide the development and implementation of an audit-based intervention tool for use in primary care settings to assist practitioners in identifying and managing AF.

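### The DOAC versus warfarin outcome models name no practice term, although patients come from over 300 practices and the protocol recognises that prescribing varies between practices

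*Protocol article*

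**What the plan says.** The Introduction gives the primary objective as a comparison of stroke and all-cause mortality between patients newly diagnosed with AF who are treated with DOACs and those treated with warfarin. The records come "from more than 3.5 million patients and over 300 general practices in England" (Data Source).

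The Covariates section sets out the adjustment item by item:

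- "We included variables likely to be used as indicators in prescribing anticoagulants: age-band, gender, and deprivation reporting Index of Multiple Deprivation (IMD) quintile";
- comorbidities, "namely, heart failure, hypertension, stroke or transient ischemic attack, and myocardial infarction or peripheral vascular disease at baseline";
- and "We also included smoking status as a covariate".

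The Statistical Analysis section names three outcome analyses. Two are in one sentence: "We studied the influence of the anticoagulation regimen by evaluating the cause-specific hazard ratio and the subdistribution hazard ratios of both events". The third follows: "Additionally, we estimated cumulative incidence for both events by direct regression, utilizing the inverse of the probability of censoring weights method". No stratum, random effect, frailty or clustered variance for practice is attached to any of them.

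Practice comes up once more in connection with the quantitative analysis. The Discussion raises missing or incomplete data as a possible problem and proposes to lessen it by an ontological approach, "considering practice level variations in the anticoagulation prescribing".

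**The concern.** The authors recognise that anticoagulant prescribing varies between practices. In a comparison of anticoagulants, that is variation in the exposure itself. It is mentioned as part of a missing-data remedy and does not reappear in the models that estimate the drug effect.

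Two separate things are at stake.

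- **Confounding by practice.** Practices that lean towards one drug may also differ in baseline risk, quality of AF care or completeness of recording. If they differ beyond what age-band, gender, deprivation, comorbidity and smoking capture, part of that difference is credited to the drug. The bias can go either way.
- **Interval width.** If drug choice and outcome both cluster within practices, a variance that treats patients as independent is too small.

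**Working it through.** The document gives no Phase 1 sample size, event count, significance level or intracluster correlation, so there is no stated figure to reproduce. Apart from the number of practices, every input below is an assumption.

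**Step 1. Interval width.** For a patient-level exposure that clusters by practice, the approximate design effect is

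DEFF = 1 + (m − 1) × ρx × ρy,

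where m is the number of anticoagulant starters per practice, ρx the intracluster correlation of drug choice and ρy that of the outcome. The correct standard error is √DEFF times the unclustered one. The actual error of a nominal 5% two-sided test is 2 × [1 − Φ(1.96/√DEFF)].

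| Case | m | ρx | ρy | DEFF | SE factor | Actual error |
|---|---|---|---|---|---|---|
| Low | 50 | 0.1 | 0.005 | 1 + 49 × 0.0005 = 1.0245 | 1.012 | 5.3% |
| Middle | 100 | 0.2 | 0.01 | 1 + 99 × 0.002 = 1.198 | 1.095 | 7.3% |
| High | 150 | 0.3 | 0.02 | 1 + 149 × 0.006 = 1.894 | 1.376 | 15.4% |

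A second grid used m = 20 to 200, ρx = 0.05 to 0.20 and ρy = 0.005 to 0.05. The SE factor ran from 1.002 to 1.73, and coverage of a nominal 95% interval from 94.9% down to 74.3%. In 20 of the 24 grid settings with ρy of 0.01 or less, the factor stayed below 1.05. The effect is large only when practices are large and both correlations are high.

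**Step 2. Confounding by practice.** A simulation took 300 practices with 50 patients each, 3 years of follow-up, an event rate of 0.05 per year and a true hazard ratio of 1. The practice log-hazard had SD 0.1 to 0.3 and the practice prescribing logit SD 0.5 to 1.0. There were 400 replicates per setting, so a coverage near 95% has a Monte Carlo standard error of √(0.95 × 0.05/400) ≈ 1.1 percentage points. Patient covariates were not simulated; the practice effect stands for what remains after adjustment.

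| Correlation of practice preference with practice risk | Mean HR | Coverage, unclustered SE | Coverage, practice-robust SE |
|---|---|---|---|
| 0 | 0.996 to 1.002 | 92% to 96% | 93% to 96% |
| +0.3 or −0.3 | 0.93 to 1.08 | 56% to 96% | 61% to 96% |

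In the most extreme positive setting (log-hazard SD 0.3, logit SD 1.0, correlation +0.3) the mean HR was 1.077. The bias is ln 1.077 = 0.074, against an unclustered standard error of 0.0431, or about 1.7 standard errors.

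Two results follow. Without a link between preference and risk there is no bias. With a link there is bias, and a clustered variance barely helps, because it widens the interval around the wrong centre.

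**The case against.** The strongest reply is that this is a condensed article, and the variance estimator is the kind of detail a fuller plan would hold. That is fair: silence on robust standard errors is weak evidence, and nothing in the text says that patients are treated as independent. It carries less weight for confounding, because the adjustment set is itemised and practice is not on it.

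Three stronger readings are tempting, and the document does not support them.

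- **That practice is ignored altogether.** The Discussion sentence shows otherwise. The gap is that the sentence is tied to missing data and to no outcome model.
- **That recording of stroke and death is known to vary between practices.** The Exposures and Outcomes section says only that published Read codes are used. The dashboard is about practices' AF data quality, and one usability task compares a practice with the network, but neither documents variation in outcome coding.
- **That the drug effect is biased and the intervals are certainly too narrow.** Bias requires prescribing preference to be related to residual practice risk after adjustment for deprivation, age, smoking and comorbidity. The document shows no such relation. The loss of interval width is small in most of the assumed settings.

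It is also fair to object that within-practice comparison has its own hazard. The data cover 2009 to 2019, and the Introduction says that DOACs changed how AF is managed. Within one practice, DOAC versus warfarin could become partly later versus earlier patients. That stands, and the remedy must allow for it.

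**Conclusion.** The point holds in a conditional form. Practice-level variation in prescribing is acknowledged but not carried into the stated adjustment set or the three outcome models.

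- **Bias.** It is possible in either direction if practice preference is associated with practice risk or recording beyond the listed covariates. Its size cannot be derived from the document. Under the simulated correlations of ±0.3, a true hazard ratio of 1 appeared as 0.93 to 1.08.
- **Precision.** Where exposure and outcome both cluster, the correct standard error exceeds the unclustered one by about 1% to 38%, with 9% in the middle case. The upper figure needs all three assumed maxima at once.

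This is worth changing because the stated models could neither reveal nor remove a practice effect. It does not show that the comparison is invalid.

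**What to change.** State how practice enters the outcome analysis, and specifically:

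1. Use practice-clustered variance in all three outcome models.
2. Add a cause-specific model stratified by practice, or with a practice frailty, and report it beside the unstratified estimate. Stratification is the cleaner choice against confounding, since an ordinary frailty assumes that the practice effect is unrelated to drug choice.
3. Account for calendar period of initiation in that model, so that within-practice contrasts are not merely earlier against later patients.
4. For the subdistribution and cumulative-incidence models, say that clustered variance corrects width only. To address confounding there, also stratify by practice or adjust for the practice-level DOAC prescribing share.
5. Reword the Discussion sentence so that it says which model takes up practice-level variation in prescribing.

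The cost is a modest re-analysis, since the article reports the Phase 1 analysis as completed in December 2019. A practice identifier should be available, because the data are uploaded by practice and the dashboard shows each user their own practice's indicators. Intervals will be slightly wider, and practices that use only one drug class add no information on the drug effect in the stratified model.
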